Despite the first report of success from quilting sutures in 1993, this technique is still not embedded in global daily practice [23]. Surgeons are reluctant to implement the quilting technique because of hypothetical disadvantages of quilting. In the absence of well-founded studies, critics are raised such as increased postoperative pain and decreased shoulder function caused by tight sutures, concerns exist about cosmetic outcome and possible skin dimpling and longer operating time could give raise to increased healthcare costs [16, 24].

To date, no multicenter prospective studies have been published in which quilting without postoperative wound drain is compared with conventional wound closure with postoperative wound drain, reporting on seroma and other potential (dis)advantages.

The objective of this study is therefore, to assess the impact of quilting in patients undergoing mastectomy and/or ALND in nine teaching hospitals. Postoperative complications, shoulder function, cosmetic outcome, satisfaction with thoracic wall, postoperative pain and healthcare consumption of patients treated with the quilting suture technique without drain will be compared with conventional wound closure. All these will be summarized in the primary outcome as textbook outcome. Textbook outcome is achieved if a patient suffers no wound complications, requires no re-admissions or re-operation in relation to primary surgery nor any unscheduled visit to the outpatient clinic and the postoperative use of analgesics after six months is not increased compared to pre-operative.

Textbook outcome is defined as the percentage of patients for whom all desired short-term outcomes of care are realized [25]. This outcome provides a meaningful summary measure of health care quality for patients, providers and insurance companies. It is a useful outcome to make a comparison between different hospitals. Usually significant variability between hospitals can be expected, all scoring well on different single factors, but poorly in other factors. Besides, a compound indicator reflecting the ideal surgical outcome is more meaningful than one single outcome item and it is a useful tool for managing patient expectations [26].

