### Objectives {7}

The objective is to report whether implementation of quilting in breast cancer surgery improves textbook outcome. Data is collected on the incidence of seroma and other postoperative complications, postoperative pain, shoulder function and health care consumption.

We hypothesize that implementation of quilting in breast cancer patients undergoing mastectomy and/or an axillary lymph node dissection increases textbook outcome. We expect incidences of seroma and other postoperative wound complications to decrease, with the same cosmetic outcome and without an increase in postoperative pain or impairing shoulder function. Moreover we hypothesize health care costs to reduce as a result of quilting.

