#### Secondary study parameters/endpoints

Wound complications are defined by the Clavien Dindo classification of Surgical Complications [27] and scored when necessitating (bed side) treatment or follow-up with additional visits to the outpatient clinic, also if beyond 30-days postoperative.All palpation-detected seromas (non-aspirated), proportion (%)Clinical significant seroma (aspirated seroma), proportion (%)Surgical site infections (SSI), proportion (%)Wound hematoma or bleeding, skin flap necrosis, wound dehiscence, visualized by inspection, proportion (%)

Health care consumption:Duration of surgery: time from incision till wound closed (minutes), meanDuration of hospital stay (treatment in day care or amount of nights, day care classified 0), meanNumbers of unscheduled visits to the outpatients clinic (one postoperative visit is scheduled), medianReadmission to the hospital related to primary surgery, medianReoperation, related to primary surgery other than re-excision, median

Baseline characteristics based on assumed risk factors for formation of seroma [3, 4, 28–31]:Biological gender, proportion (%)Age (years at day of surgery), meanBMI (kg/m^2^), meanWeight of the removed breast (gram), meanPolypharmacy (use of five or more medications daily [32], proportion (%)TNM classification (type 1 to 4, no malignancy, in situ, ypT0N0, angiosarcoma), nominal, proportion per stage (%)Type of surgery (uni- or bilateral mastectomy, ALND or a combination), nominal, proportion per type (%)Prior irradiation of the breast in recurrent breast cancer, proportion (%)Neoadjuvant chemotherapy, proportion (%)

Other:Shoulder function questionnaire (DASH questionnaire = Disability of the Arm, Shoulder and Hand [33], median scorePost-operative pain (visual analogue scale day 1–14 postoperative and use of analgesics), median scoreCosmetic outcome (an independent panel of four surgeons will blindly assess cosmetics by classifying standardised digital photographs one a 4-point Likert scale with the following categories: poor, fair, good and excellent. Photos are taken in two positions: the first in neutral position with both arms hanging next to the body and the second with both arms raised in 180gr (or as far as possible) elevation).Satisfaction with thoracic wall (BreastQ questionnaire for mastectomy [34]), median score

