### Statistical methods

#### Statistical methods for primary and secondary outcomes {20a}

Primary outcome is a binary outcome presented as number of cases and percentage. Nominal data will also be presented as percentage. Continuous data will be presented as mean ± standard deviation or median ± interquartile range, based upon whether the assumption of normality holds (visual interpretation). Analysis of continuous data will be performed by applying the Students T-test for unpaired data in case of continuous variables with a normal distribution. Otherwise the distribution will be compared using the Mann–Whitney U-test. Chi2 test will be used for comparisons of categorical variables between the two groups. The Fisher’s exact test will be performed where applicable. Since data is clustered analysis will be performed using a generalized logistic mixed-effects model with cluster as random intercept. A P-value < 0.05 is considered statistically significant.

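### Cosmetic outcome is an ordered four-level scale, but the analysis section names no method that uses the order and gives a direction and size of effect

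*Protocol article*

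**What the plan says.** Protocol article, Secondary study parameters/endpoints: "an independent panel of four surgeons will blindly assess cosmetics", using standardised photographs graded on a "4-point Likert scale with the following categories: poor, fair, good and excellent". The DASH, pain and BreastQ items in the same list are each to be summarised by a median score. Cosmetic outcome has no summary measure.

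Protocol article, Statistical methods for primary and secondary outcomes {20a}, gives three instructions that could apply:

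- Continuous data go to the t-test if normal. "Otherwise the distribution will be compared using the Mann–Whitney U-test".
- "Chi2 test will be used for comparisons of categorical variables between the two groups", with Fisher's exact test where applicable.
- "Since data is clustered analysis will be performed using a generalized logistic mixed-effects model with cluster as random intercept". The sentence does not say which outcomes it covers.

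Ordinal data are not mentioned, and no sentence names the test for cosmetic outcome itself.

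The background section {6a} gives the reason for measuring it: "concerns exist about cosmetic outcome and possible skin dimpling". The objectives {7} expect quilting to come "with the same cosmetic outcome and without an increase in postoperative pain".

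**The concern.** The four grades run from worst to best, and the question has a direction: does quilting make the result look worse? A Pearson chi-square on a 2 × 4 table has 3 degrees of freedom. It gives the same p-value if the grade labels are shuffled. It cannot say whether cosmesis improved or worsened, and it yields no effect size with an interval.

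That matters because the expected answer is no difference. Under the rule "A P-value < 0.05 is considered statistically significant", a non-significant chi-square could be taken as support for equal cosmesis, although nothing reported would show how much worsening the data still allow. Cosmesis is one of the concerns that the article says make surgeons reluctant to adopt quilting, so readers will look for this result.

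**Working it through.** **1. Which method applies.**

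| Reading of {20a} | Method for the four grades | Uses order? | Direction and estimate? |
|---|---|---|---|
| Categorical rule | Chi-square or Fisher | No | No |
| Mixed-model sentence | Logistic mixed model | Only with an unstated cut-point or an unstated ordinal extension | Depends on that choice |
| Continuous rule | Mann–Whitney or t-test | Yes | Not stated; needs the grades treated as continuous, or a combined score that the article does not define |

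The article calls the grades categories and gives no median or mean for them, so the first row is the most natural reading. It is an inference from the general rule.

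**2. Inputs for the power comparison.** The article gives no power figure and no grade distribution for cosmetic outcome, so there is no stated figure to reproduce. From the sample size section {14}: 94 patients before the margin, and 94 × 1.2 = 112.8, so 113 after it. Assumptions:

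- Equal split: 94/2 = 47, or 113/2 ≈ 56, per condition.
- One grade per patient, two-sided 0.05, independent patients (no clustering, no period effect).
- Four conventional-closure distributions, poor to excellent: 10/20/40/30, 5/15/50/30, 25/25/25/25 and 10/30/45/15%.

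**3. Worsening spread evenly over the scale.** The odds of each cumulative proportion are multiplied by a common odds ratio (OR). Example, 10/20/40/30% with OR 2:

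- 0.10 → odds 0.111 × 2 = 0.222 → 0.182
- 0.30 → odds 0.429 × 2 = 0.857 → 0.462
- 0.70 → odds 2.333 × 2 = 4.667 → 0.824

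Quilting is then 18.2/28.0/36.2/17.6%. Simulated power, range over the four distributions (8,000 runs each):

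| OR | 47 per group: chi-square / Mann–Whitney | 56 per group: chi-square / Mann–Whitney |
|---|---|---|
| 2 | 28–31% / 43–46% | 32–36% / 48–52% |
| 2.5 | 46–51% / 64–69% | 55–59% / 73–76% |
| 3 | 64–67% / 80–83% | 71–76% / 86–89% |

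Within one distribution the gap is about 13 to 18 points, with simulation error of about half a point on each power. At OR 1 both tests reject in about 5% of runs.

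**4. Analytic check.** A 1-df test with 80% power has noncentrality (1.960 + 0.842)² ≈ 7.85. The same noncentrality on 3 df gives 64% power. Reaching 80% on 3 df needs 10.90, and 10.90/7.85 = 1.39, so about 39% more patients.

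**5. Worsening concentrated in the lowest grade.** In each row below, every cumulative proportion under quilting is equal to or worse than under conventional closure, so each is a true worsening.

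| Conventional (%) | Quilting (%) | n per group | Chi-square | Mann–Whitney |
|---|---|---|---|---|
| 10/20/40/30 | 30/10/30/30 | 56 | 69% | 21% |
| 10/20/40/30 | 25/20/25/30 | 56 | 50% | 26% |
| 10/25/45/20 | 30/25/25/20 | 47 | 63% | 45% |
| 10/25/45/20 | 25/20/35/20 | 47 | 34% | 19% |
| 10/25/45/20 | 30/15/35/20 | 47 | 58% | 23% |

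Here the order of the two tests reverses.

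**The case against.** The strongest objections are these.

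- **No test is assigned to cosmetic outcome.** Correct. Chi-square follows from the general rule, not from a sentence about this outcome. If the four surgeons' grades were averaged or summed, the continuous route, including the rank test, could apply. The article does not state such a score, and the full protocol may, so the missing combining rule is not held against the article. What stands is that the rules as printed send four named categories to a test that ignores order.
- **The mixed-model sentence covers secondary outcomes and yields an odds ratio.** It may well cover them, since it sits under the heading for both kinds of outcome. But a binary logistic model needs two levels. Any cut-point or ordinal extension is unstated, and dichotomising would discard part of the scale.
- **An analysis plan can settle this.** It can. The point here is that the article fixes a general rule that fits this scale badly, and a later document would have to depart from it.
- **The power loss depends on the pattern of harm.** Correct, and it limits the point. A reader might infer that chi-square misses any real cosmetic harm more often. The calculations do not support that. The Discussion mentions dimpling where the subcuticular layer is thin, so a subset could drop to the lowest grade, and there chi-square can detect more.

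**Conclusion.** The point holds in a limited form. The outcome is ordered and the article names no ordinal method for it. The categorical rule gives no direction and no effect estimate, and a binary logistic model does not fit four levels. Those statements need no power assumption.

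The loss of about 13 to 18 points applies to a roughly even shift with 47 to 56 patients per condition. It rests on assumed distributions and odds ratios, an equal split, and no clustering or period effect. It therefore shows the relative loss between two tests, not the power the trial will have.

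Two stronger readings are not supported: that the article expressly assigns chi-square to cosmetic outcome, and that chi-square is always the less sensitive test. This is a secondary outcome with no power claim attached. The change is worth making, but the primary analysis does not depend on it, and no clinical management is involved.

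**What to change.** In the statistical methods section {20a}, state that:

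- Cosmetic outcome is analysed as ordinal with a cumulative-logit mixed model, with a hospital random intercept and a calendar-period term. The period term is needed because, in a stepped wedge, quilting becomes more common as calendar time passes.
- The four surgeons' ratings enter through patient and rater effects, or through one prespecified combined score.
- The report gives the common odds ratio with its 95% confidence interval, and the percentage in each grade by condition, including the proportion graded poor, so that an uneven shift is visible.
- Chi-square and Fisher's exact test are kept for unordered or two-level variables.

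The cost is a few lines of text and somewhat more modelling, with no extra patients, photographs or raters. With nine hospitals and about 113 patients, the combined score is the simpler choice if the model with patient and rater effects proves hard to fit. The downside is that the common odds ratio assumes a roughly constant shift over the scale. The percentages per grade let the reader check that assumption.

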### Cost analysis

The cost analysis exists of two main parts. First, volumes of care will be measured prospectively using medical records, resource uses such as visits to the outpatient clinic, medication, hospital (re)admissions and surgical interventions (including intraoperative materials, disposables and operation time). Per arm (Quilt vs drain) full cost-prices will be determined using activity based costing. The second part of the cost analysis consists of determining the cost prices for each volume of consumption in order to use these for multiplying the volumes registered for each participating patient. The Dutch guidelines for cost analyses will be used [38]. For units of care/resources where no guideline or standard prices are available real cost prices will be determined.

Economic analysis will be performed by a specialized statistician.

### Interim analyses {21b}

Not applicable.

### Methods for additional analyses (e.g. subgroup analyses) {20b}

Not applicable.

### Methods in analysis to handle protocol non-adherence and any statistical methods to handle missing data {20c}

Stochastic regression imputation will be used to impute missing data.

Patients lost to follow up will be excluded from the study.

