### Sample size {14}

To calculate the sample size of a randomized controlled trial TO is assumed to be 30% without quilting, as based upon a pilot study [7]. A doubling of TO is considered clinically significant, resulting in a TO of 60% with quilting. In this study 2 treatment arms will be used, with a significance level of 0.05 and power of 80%. For a parallel randomized trial in which *patients* are randomized, a minimum of 44 patients need to be included:$$2* {\left({\mathrm{Z}}_{\frac{0.05}{2}}+{\mathrm{Z}}_{0.80}\right)}^{2}*\frac{1}{{0.30}^{2}}* 0.45\left(1-0.45\right)=44$$

However, since in the present study *clusters* and not patients are randomized, we need to correct for the fact that outcomes within clusters are very likely more similar than those between clusters. The degree of similarity is estimated using the intra-cluster correlation coefficient (ICC) [35]. This was estimated to be on average 0.028, based upon the pilot study of the 2 hospitals with the variables age, body weight, ASA classification, type of surgery, neo-adjuvant chemotherapy, radiotherapy, tumour classification and first or second episode of breast cancer.

Consequently, the formula as proposed by Hemming et al. was used to correct for this similarity with a total of nine clusters and nine steps [36]. This led to a minimum of 94 patients in total or 11 per centre. A margin safety of 20% was introduced to correct for loss-to-follow-up, which led to a total of 113 patients or 13 per centre. Based on an average of 50 mastectomies each year per centre, the duration of the total inclusion should take 3 months. To correct for the probability of non-adherence to the quilting technique since it is new implemented for all surgeons (safety margin of 20%) each step will take 2 weeks. Suspected transition period and learning curve was suspected to be eight weeks.

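### Stochastic regression imputation without pooling treats imputed values as observed, so standard errors and p-values come out too small, mainly for the questionnaire outcomes

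*Protocol article*

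**What the plan says.** The protocol article has two sentences on missing data, in section {20c}. The first names the method: "Stochastic regression imputation will be used to impute missing data". The second removes one group from its reach: "Patients lost to follow up will be excluded from the study". No number of imputed data sets, pooling rule, bootstrap or other variance correction is given.

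Section {20a} plans t-tests, Mann–Whitney tests and chi-square or Fisher tests. For the clustered data it plans a "generalized logistic mixed-effects model with cluster as random intercept". The threshold is stated without qualification: "A P-value < 0.05 is considered statistically significant".

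Under Outcomes {12}, textbook outcome has five components. Four are clinical events, and the fifth compares analgesic use at six months with use before surgery. The Participant timeline {13} collects analgesic use, DASH and BreastQ by questionnaire, and VAS as a daily patient entry for two weeks. Section {18b} anticipates unreturned questionnaires and plans telephone contact.

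The only allowance for lost data is in Sample size {14}: "A margin safety of 20% was introduced to correct for loss-to-follow-up".

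**The concern.** The random residual in stochastic regression imputation preserves the spread of the data, which is its advantage over filling in the predicted mean. It does not tell the later analysis that some values were invented. Two sources of variance go missing: the information came from fewer real observations than the analysis counts, and the random draw adds noise of its own. The point estimate can still be unbiased if data are missing at random, but intervals are too narrow and the stated significance level is exceeded.

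With a target of 113 patients, a single draw can also carry a borderline p-value across 0.05, so the result may depend on the random seed. What is at stake is the error rate of the between-group comparisons. These include the questionnaire results on shoulder function, pain and satisfaction, which the trial needs in order to answer the doubts about quilting described in its introduction.

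**Working it through.** **The plan's own figures.** The plan gives no figure for imputation. The one related number is the 20% margin in {14}: 94 × 1.20 = 112.8, rounded to 113. It adds patients to replace those lost. Because {20c} excludes lost patients, they are not imputed, and the margin says nothing about how many values will be. The fraction imputed, f, is therefore an assumption, taken here as 5% to 30%.

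**Other inputs.** Two-sided 5% level ({20a}; the formula in {14} uses the 0.05/2 quantile). "TO is assumed to be 30% without quilting" and "resulting in a TO of 60% with quilting" ({14}), with 45% as their midpoint. 94 patients before the margin, so 47 per group.

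**Step 1: a whole outcome imputed once, without predictors.** Values are missing completely at random, n patients, variance σ².

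- The mean rests on n(1 − f) real values: σ²/[n(1 − f)].
- The nf random residuals add nf·σ²/n² = fσ²/n.
- The analysis reports σ²/n.

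True variance / reported variance = V = 1/(1 − f) + f. Real type I error = 2[1 − Φ(1.96/√V)].

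| f | V | Reported SE / true SE | Type I error, formula | Type I error, simulation |
|---|---|---|---|---|
| 5% | 1.053 + 0.05 = 1.103 | 0.95 | 6.2% | 6.2–6.3% |
| 10% | 1.111 + 0.10 = 1.211 | 0.91 | 7.5% | 7.3% |
| 20% | 1.250 + 0.20 = 1.450 | 0.83 | 10.4% | 10.2–10.3% |
| 30% | 1.429 + 0.30 = 1.729 | 0.76 | 13.6% | 13.9–14.2% |

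The simulation used 47 per group, no true effect, outcome rates of 30% and 45%, a z-test and 40,000 runs. In the same runs, multiple imputation (20 sets, Rubin's rules) gave 5.1–5.5% and complete cases gave 5.0–5.3%.

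**Step 2: with a useful predictor.** If the imputation model explains a share R² of the outcome's variance, and the analysis does not itself adjust for that predictor, only the unexplained part is affected:

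V = 1 + (1 − R²)[1/(1 − f) + f − 1].

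As an illustration, take R² = 0.5 (assumed). At f = 20%, V = 1 + 0.5 × 0.45 = 1.225 and type I error is 7.7%. At f = 10%, V = 1 + 0.5 × 0.211 = 1.106 and type I error is 6.2%. DASH and BreastQ have pre-operative values that can play this part. The timeline lists no pre-operative VAS.

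**Step 3: textbook outcome.** Suppose that only the analgesic item is missing and that it is imputed as an item. A patient who fails any other component is already known not to have a textbook outcome, so the imputed value matters only for the rest. Null simulation, 47 per group, items independent (assumed), with an assumed share of patients passing the analgesic item:

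| Textbook outcome rate | Share passing the item | 10% of items missing | 20% of items missing |
|---|---|---|---|
| 30–45% | 80–95% | 4.9–5.5% | 5.1–5.9% |
| 30–45% | 70% | 5.6–5.8% | 6.1–6.8% |
| 60% | 70% | about 6.5% | about 8% |

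These figures estimate the item's pass rate from all retained patients in the group. Estimating it only among those who passed the other components uses fewer observations and gives somewhat higher values. All the simulations leave out clustering and time, to isolate the imputation effect.

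**The case against.** **The number of draws is not stated.** This is a condensed article, and an analysis plan that is not shown could add repeated imputation and pooling. That is fair, and single imputation is read here from the method's usual meaning. Still, the article did not leave the matter open: it named a method, and nothing in it points to repeated draws.

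**The 20% margin.** A reader might take the 20% in {14} as the fraction to be imputed and conclude that the primary test runs at about 10%. The documents do not support this. The margin is for loss to follow-up and those patients are excluded, so the 20% rows above are scenarios.

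**Reach to the primary outcome.** A reader might also carry the whole-outcome figures over to textbook outcome. Four of its components are clinical events, {18a} takes outcome variables from the patient file, and the analgesic item is the one most exposed to non-response. On that reading the inflation is mostly small. Imputing textbook outcome as a single yes/no variable would be worse, but the article does not say that this will be done.

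**Predictors.** The formula without predictors is an upper bound where baseline scores predict well. This stands, and Step 2 shows by how much.

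**The remedy.** A rich imputation model could overfit or fail through separation: 113 patients over nine hospitals and nine steps is 113/81 ≈ 1.4 per hospital and step. This also stands, and it shapes the fix.

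**Conclusion.** The point holds. As written, the plan analyses imputed values as if they had been observed, so standard errors and p-values are too small. The direction is clear. The size depends on a missing fraction that the documents do not give.

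- For an outcome imputed whole and without useful predictors, the real error rate is about 6% at 5% missing, 7.5% at 10% and 10% at 20%. Good baseline predictors lower this.
- For textbook outcome with only the analgesic item imputed, it is about 5–7% at rates of 30–45%, and up to about 8% at 60% with 20% missing.

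The main exposure is therefore in DASH, BreastQ and VAS, and the effect on the primary test is probably modest. These figures assume values missing completely at random, no clustering and, for textbook outcome, independent components. The sentence should be changed before analysis, but the flaw does not by itself undermine the primary comparison.

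**What to change.** Replace the sentence on stochastic regression imputation with multiple imputation, for example 20 to 50 data sets.

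- Impute textbook outcome at component level and derive the composite afterwards, so that a patient who has failed a known component is never imputed as a success.
- Keep the imputation model small: condition (quilting or conventional closure), hospital as a random effect or similar, a simple time term and the baseline value of the outcome where there is one.
- Fit the planned model in each data set and combine the results with Rubin's rules.
- Report the fraction imputed for each outcome.

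The cost is one changed sentence, a little more analysis work and slightly wider intervals. Care is needed with sparse hospital-period cells, which is why the time term should be simple and hospital should not enter as a full set of interactions. No new data are needed, and patient care does not change.

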### Outcomes {12}

#### Primary study parameter/endpoint

‘Textbook outcome’ (TO), a combination of outcome parameters reflecting an ideal surgical outcome. Measured 6 months post-operative, the patients postoperative course must comply with the following to meet the definition of TO:no wound complicationsno re-admissions in relation to primary surgeryno re-operation in relation to primary surgery, re-excisions in case of involved margins allowedno unscheduled visit to the outpatient clinic (depending on the centre one or two postoperative visits are usually scheduled)postoperative use of analgesics (6 months) is not increased compared to pre-operative

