### Participant timeline {13}

Participation burden consists of filling out questionnaires. The first questionnaires (t = 0 pre-operative) are handed out pre-operatively, (DASH, use of analgesics, BreastQ). Patients are asked to notate the VAS daily during the first two weeks postoperative. Two weeks postoperatively, at scheduled postoperative evaluation, participants will be evaluated by physical examination, a picture of the amputated breast will be taken by the treating surgeon or breast cancer nurse, combined with the DASH questionnaire and use of analgesics again (t = 1). Follow-up lasts for 6 months postoperatively when another picture of the amputated breast is taken and the final DASH and analgesic are completed (t = 2). Additionally, the BreastQ mastectomy module is questioned (Table 1).

**Table 1 Tab1:** Participant timeline

	**Enrolment**	**Operation**	**Days 1–14 postoperative**	**2 weeks postoperative**	**6 months postoperative**
Patient information form	X				
Letter of objection	X				
Physical examination				X	X
Picture of the thoracic wall				X	X
Questionnaires - DASH - Use of analgesics - Breast Q	X			X	X
VAS pain scores			X		

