### Data collection and management

#### Plans for assessment and collection of outcomes {18a}

Outcome variables are extracted from the electronic patient file by the local investigator.

Baseline characteristics and variables of health care consumption will be collected by data managers.

Data collection forms are constructed in Castor, questionnaires will also be registered in Castor, questionnaires can be sent digital from Castor depending on patients preference.

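### Excluding every patient lost to follow-up discards textbook-outcome failures already on record, and can bias the comparison if loss depends on outcome

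*Protocol article*

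**What the plan says.** Section {20c} of the protocol article contains two sentences. The first is "Stochastic regression imputation will be used to impute missing data". The second is "Patients lost to follow up will be excluded from the study". It carries no qualification.

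The primary endpoint, in section {12}, is a composite measured six months after surgery: "the patients postoperative course must comply with the following to meet the definition of TO". Five conditions follow: no wound complication, no related re-admission, no related re-operation (re-excision for involved margins is allowed), no unscheduled outpatient visit, and "postoperative use of analgesics (6 months) is not increased compared to pre-operative".

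On data sources, section {18a} says "Outcome variables are extracted from the electronic patient file by the local investigator". The participant timeline in section {13} has the analgesic item completed alongside the last DASH questionnaire at six months.

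**The concern.** TO is all-or-nothing and its failures cannot be undone. Consider a patient whose seroma is aspirated in week 3 and who then never returns the six-month form. Her primary outcome is known: TO was not achieved. Read literally, the exclusion sentence removes her. A patient who was event-free up to last contact is removed as well, although most of her outcome is also known.

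Two things are at stake. Valid primary-outcome data are discarded in a trial of only 113 patients. In addition, if the chance of being lost differs between patients who fail and patients who achieve TO, the remaining sample misstates the TO rate. If that pattern also differs between the conventional and quilting phases, the treatment comparison moves. The study is unblinded and its follow-up relies partly on questionnaires and photographs, so such dependence is possible, but the article gives no data on it.

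The exclusion also sits uneasily beside the imputation sentence. The article does not show where missing data end and loss to follow-up begins, so a missed six-month questionnaire could lead to either imputation or deletion.

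**Working it through.** **Inputs from the article.** From section {14}: "TO is assumed to be 30% without quilting", 60% with quilting, 94 patients before and 113 after a 20% allowance for loss. The loss rates by outcome below are assumptions; the article gives none.

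**The plan's own figure.** 94 × 1.20 = 112.8, rounded up to 113, which reproduces the article. The allowance is 113 − 94 = 19 patients, or 19/113 = 17% of those included.

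**How many of the 19 could be known failures.** Take two phases of equal size and loss unrelated to outcome. The failure rate is (0.70 + 0.40)/2 = 0.55, that is, a mean TO of 45%. Then 19 × 0.55 = 10.45, about 10 patients. This is an upper bound on known failures, because some patients fail after last contact or through analgesic use alone.

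**Effect of deletion on an observed TO rate.** Let p be the true TO rate, L1 the loss among achievers and L0 the loss among failures:

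observed TO = p(1 − L1) / [p(1 − L1) + (1 − p)(1 − L0)]

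- p = 0.30, L1 = 0.10, L0 = 0.25: 0.270/(0.270 + 0.525) = 0.270/0.795 = 34.0%.
- p = 0.30, L1 = 0.25, L0 = 0.10: 0.225/(0.225 + 0.630) = 0.225/0.855 = 26.3%.
- p = 0.60, L1 = 0.10, L0 = 0.25: 0.540/(0.540 + 0.300) = 0.540/0.840 = 64.3%.
- p = 0.60, L1 = 0.25, L0 = 0.10: 0.450/(0.450 + 0.360) = 0.450/0.810 = 55.6%.
- L1 = L0: the loss terms cancel and observed TO = p, so there is no bias.

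**Effect on the difference (true value 30 points).**

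- Failures lost more often in both phases: 64.3 − 34.0 = 30.3.
- Achievers lost more often in both phases: 55.6 − 26.3 = 29.3 from the rounded rates.
- Failures lost more often under conventional closure, achievers more often under quilting: 55.6 − 34.0 = 21.6.
- The opposite: 64.3 − 26.3 = 38.0.

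Opposite patterns thus move the difference by about 8 points either way. With no true effect (30% in both phases) they would create a gap of 34.0 − 26.3 = 7.7 points.

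**Sensitivity, with overall loss fixed at 20% in each phase.** Here observed TO = p(1 − L1)/0.80, with L1 = [0.20 − (1 − p)L0]/p.

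- L0 = 25% in both: 34.4% vs 62.5%, difference 28.1.
- L0 = 10% in both: 21.3% vs 55.0%, difference 33.8.
- L0 = 25% conventional, 10% quilting: 34.4% vs 55.0%, difference 20.6.
- L0 = 10% conventional, 25% quilting: 21.3% vs 62.5%, difference 41.3.

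**Check of two half-measures.** Assume 20% random loss, p = 0.30 and all failures visible in the file.

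- Keep the known failures but delete the event-free lost patients: achievers retained 0.30 × 0.80 = 0.24, failures 0.70, so 0.24/0.94 = 25.5% instead of 30%.
- Impute the whole of TO for event-free lost patients at the overall rate: 0.24 + 0.06 × 0.30 = 25.8% instead of 30%.

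Under the same random loss, plain deletion would be unbiased. The remedy therefore has to use the fact that these patients were event-free.

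**The case against.** Several counter-arguments have force.

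First, a reader might infer that the two sentences in {20c} contradict each other. They need not: they can be read as a two-level rule, imputing missing items for patients who are followed and excluding patients who are lost. That reading is coherent. What remains is that the boundary is not visible in the article. Section {18b} provides telephone contact and several routes for retrieving questionnaires, so a patient with a file but no form might count merely as having missing data. The full protocol may define this. Even on the narrow reading, a lost patient with a failure already on file is still removed.

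Second, it is tempting to say that four of the five components come from the file. Section {18a} does not list the variables, and Table 1 schedules a physical examination at six months, so detection of late wound problems partly depends on attendance. This limits how many failures are known at the time of loss, which is why 10 of 19 is only an upper bound. It does not undo a failure already recorded.

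Third, a reader might say that the rule breaks an intention-to-treat comparison. The article declares no such analysis, and section {11b} already excludes patients whose surgeon refrains from quilting, so that charge is not supported.

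Fourth, every loss pattern used above is assumed. With the same assumed pattern in both phases, the difference moves by less than 4 points. The larger shifts need opposite patterns, for which the article offers no evidence.

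Finally, patients may object to the processing of their medical data (sections {26a} and {26b}), so keeping literally everyone would go too far.

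**Conclusion.** The point stands in a limited form. As written, the exclusion discards patients whose primary outcome is already determined, up to about 10 of the 19 losses allowed for among 113 patients. That number assumes equal phases, loss unrelated to outcome and failures visible before loss.

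Bias is possible but not established. There is none if loss is independent of outcome within each phase, and the direction is open otherwise. The article does not support a statement that the result will be biased, or that it will favour quilting. For illustration, a true 30% is seen as 34% or 26% under the assumed 25%/10% loss rates, and the phase difference shifts by about 8 points if the patterns are opposite. This is a cheap improvement, best made before analysis.

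**What to change.** Replace the exclusion sentence in {20c} with a rule along these lines:

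- Keep every included patient in the analysis, except those who object to use of their data.
- Score TO as 'not achieved' once any component failure is recorded, regardless of later follow-up.
- Where no failure is recorded, impute only the unknown component or components (such as six-month analgesic use, and events after last contact), conditional on the patient being event-free so far and on phase and cluster. Then derive TO from the completed components.
- Do not keep known failures while deleting event-free lost patients, and do not impute TO as a whole without using event-free status. Both lower TO artificially.

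The same text should state when a missed six-month contact counts as missing data and when as loss to follow-up.

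The cost is a few sentences. The planned sample size of 113 does not change, and the recorded failures are already in the hospital files. The downside is somewhat more analysis work and reliance on the imputation model, including for events after last contact or treated elsewhere.
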